### Monitoring and Oversight

DSMB constituted by the CCRAS, comprising experts in neurology, clinical trials, ethics, and Ayurveda, to oversee participant safety and trial integrity. The NIMHANS Ethics Committee will provide continuous ethical oversight. CCRAS will conduct independent monitoring for protocol, GCP, and regulatory compliance, ensuring objectivity. As an exploratory trial, no interim analysis is planned. However, the DSMB will periodically review safety data, including SAEs and potential risks, to ensure participant well-being. The DSMB, in consultation with the Institutional Ethics Committee and CCRAS, will make independent recommendations regarding trial continuation, modification, or termination. This process ensures ongoing participant safety and upholds the trial’s scientific and ethical integrity through consistent monitoring and safety oversight.

### Harms: AE Collection, Assessment, Reporting, and Management

Participants will be assessed for AEs at each scheduled follow-up visit (days 60, 120, and 180) and during routine hospital visits. Each reported AE will be documented and categorized based on severity, relatedness to the intervention, and expectedness, following standardized guidelines. Laboratory safety assessments, including liver function tests, RFTs, and complete blood count, will be performed at baseline and at the final study visit (day 180) to monitor any potential systemic effects. All recorded AEs will be reviewed by the DSMB, which will assess their clinical significance and provide recommendations for participant safety. SAEs will be promptly reported to the NIMHANS Human Ethics Committee and the sponsor, CCRAS, in accordance with regulatory guidelines.

For participants who discontinue or deviate from the intervention protocol, no further outcome assessments will be conducted, as the primary outcome (MDS-UPDRS Part III) requires evaluation in both ON and OFF medication states, and other assessments (TMS, pulmonary function tests, Montreal Cognitive Assessment, 6-m walk test, and Balance Error Scoring System) are performed in the OFF state. The reasons for nonadherence (eg, adverse effects, lack of perceived benefit, or personal constraints) and nonretention (eg, withdrawal or loss to follow-up) will be systematically documented either during the next scheduled visit or through telephonic communication. These details will be recorded in the case report forms to enable transparent reporting and analysis of participant flow and data completeness.

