Safety assessments will include monitoring for treatment-emergent adverse events throughout the study period. Liver function tests, renal function tests, and complete blood count will be performed at baseline and at the end of the study (day 180) to detect any potential systemic adverse effects. For participants undergoing Basti therapy, adverse events (AEs) will be monitored during the in-patient care.

Participants in the TAU arm will continue with their dopaminergic medications. At baseline, stabilized or optimized dopaminergic doses will be recorded, and any subsequent changes during the trial will be documented along with dates and reasons. Levodopa equivalent daily dose (LEDD) will be calculated at each visit (baseline and follow-ups) using standardized conversion factors and tracked longitudinally.

All clinical and neurophysiological outcome assessments will be performed by a trained SRF with an MD (Ayurveda) qualification, and the routine assessments will be done by the neurologists involved in the study before prescribing the study TAU interventions or deciding changes in interventions. The SRF underwent a 3-month structured training program under the supervision of a neurologist and neurophysiologist to ensure competency in administering both clinical and neurophysiological assessments. The same SRF will also be responsible for data collection throughout the study to maintain consistency.

All outcome measures are evaluated using validated clinical scales and standardized laboratory instruments, as detailed in the manuscript, each with established reliability and validity. Before the commencement of data collection, all laboratory instruments and procedures will be calibrated and standardized. To promote data quality, assessors received formal training, and interrater reliability for the primary outcome measure (MDS-UPDRS Part III) will be established in at least 20% of participants.

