#### Estimation of Cytokine by Cytometric Bead Array

Cryopreserved plasma specimens will be processed according to the manufacturer’s instructions for the detection and quantification of the proposed cytokines using the Cytometric Bead Array kit (BD Biosciences). Data will be acquired on FACS Verse flow cytometer (BD Biosciences) and analyzed on FCAP Array software (BD Biosciences Table 2).

**Table 2. T2:** Participant enrollment and schedule of assessment.

Assessments	Baseline	60th day	120th day	180th day
MDS-UPDRS^a^	✓	✓	✓	✓
UDyRS^b^	✓	✓	✓	✓
SCOPA-S^c^	✓	✓	✓	✓
MoCA^d^	✓	✓	✓	✓
6-minute walk test Gait speed (10-m walk test)	✓	✓	✓	✓
BESS^e^	✓	✓	✓	✓
Laboratory parameters				
Hematology				
Complete hemogram	✓	—^f^	—	✓
ESR^g^	✓	—	—	✓
Biochemistry				
Liver function test	✓	✓	—	✓
Renal function test	✓	✓	—	✓
Lipid profile	✓	—	—	✓
HbA_1c_^h^	✓	—	—	✓
FBS^i^	✓	—	—	✓
Sr. Uric acid	✓	—	—	✓
Inflammatory markers				
Plasma cytokine assay	✓	—	—	✓
Immunophenotyping for Th1/Th2/Th17/T-regulatory cell population	✓	—	—	✓
TMS^j^				
Single pulse measures	✓	—	—	✓
Paired pulse measures	✓	—	—	✓
Neurophysiological parameters	✓	—	—	✓
HRV^k^	✓	—	—	✓
PFT^l^	✓	—	—	✓
Concomitant medication	✓	✓	✓	✓
Rescue medication	—	✓	✓	✓

a MDS-UPDRS: Movement Disorder Society–Unified Parkinson’s Disease Rating Scale.

b UDyRS: Unified Dyskinesia Rating Scale.

c SCOPA-S: Scales for Outcomes in Parkinson’s Disease–Sleep.

d MoCA: Montreal Cognitive Assessment.

e BESS: Balance Error Scoring System.

f Not available.

g ESR: erythrocyte sedimentation rate.

h HbA_1c_: glycated hemoglobin.

i FBS: fetal bovine serum.

j TMS: transcranial magnetic stimulation.

k HRV: heart rate variability.

l PFT: pulmonary function test.

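### The Harms section stops outcome assessments after discontinuation without saying whether safety blood tests and AE review continue, so an early stopper may have no post-baseline safety blood result

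*Protocol article*

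**What the plan says.** All places are in the Protocol article.

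- **Stop rule (Harms section, second paragraph).** "For participants who discontinue or deviate from the intervention protocol, no further outcome assessments will be conducted". The reason follows: "as the primary outcome (MDS-UPDRS Part III) requires evaluation in both ON and OFF medication states". The sentence then adds TMS, pulmonary function, the cognitive test, the walk test and the balance test as OFF-state measures.
- **After stopping (same paragraph).** What is recorded is the reason: "The reasons for nonadherence (eg, adverse effects, lack of perceived benefit, or personal constraints". These reasons, and those for nonretention, "will be systematically documented either during the next scheduled visit or through telephonic communication".
- **AE schedule (Harms section, first paragraph).** "Participants will be assessed for AEs at each scheduled follow-up visit (days 60, 120, and 180) and during routine hospital visits".
- **AE period (Outcome Measures).** "Safety assessments will include monitoring for treatment-emergent adverse events throughout the study period".
- **Safety laboratory tests in the text.** The Harms section says that they "will be performed at baseline and at the final study visit (day 180) to monitor any potential systemic effects". Outcome Measures gives the same two time points.
- **Safety laboratory tests in Table 2.** The row "Liver function test" is ticked at baseline, day 60 and day 180, and so is the renal row. The complete hemogram is ticked only at baseline and day 180. As printed, the table has no row for AEs.

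**The concern.** The stop rule stands in the Harms section, directly after the AE and laboratory schedule. It applies to anyone who discontinues or deviates, and that includes people who stop because of an adverse effect. The protocol describes safety tests and AE monitoring within Outcome Measures, and no sentence exempts them from the stop. Site staff could therefore reasonably take the rule to end safety follow-up as well.

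Safety is part of the stated hypothesis, and AEs are to be summarised by treatment group. If laboratory results are missing mainly in those who stopped, the safety summary leans towards those who tolerated treatment, and the DSMB reviews the same truncated data. Only Group B has a study-specific therapy to stop, so the loss could also differ between arms.

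The word for deviation widens the reach. The section on fidelity and adherence has the intervention withheld for intolerance, fever or infection, and the text does not say whether that counts as a deviation.

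**Working it through.** **Step 1. Reproduce the participant flow (Results).** Completed + discontinued + continuing = 33 + 14 + 11 = 58, which matches the enrolled number.

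**Step 2. How many participants the rule may touch.**

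- Of all enrolled: 14/58 = 24.1% (Clopper-Pearson 95% interval 13.9% to 37.2%).
- Of those whose participation has ended: 14/(33 + 14) = 14/47 = 29.8% (17.3% to 44.9%). This leaves out the 11 still in follow-up, so it may overstate the final rate.
- Carried to the planned 80: 80 × 14/58 = 19.3 and 80 × 14/47 = 23.8, so about 19 to 24 discontinuers. The attrition allowance in Sample Size implies 80 × 0.20 = 16.

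These are counts of discontinuers. They are not counts of people without safety data.

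**Step 3. Post-baseline safety results available for someone who stops.** The stopping days are illustrations. The narrow reading stops efficacy measures only; the wide reading stops everything described in Outcome Measures.

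| Stops on | Reading | Schedule in text | Schedule in Table 2 |
|---|---|---|---|
| Day 45 | Wide | No liver, renal or blood-count result | No liver, renal or blood-count result |
| Day 90 | Wide | No liver, renal or blood-count result | Liver and renal at day 60; no blood count |
| Day 45 or 90 | Narrow, attends day 180 | Full panel at day 180 | Full panel at day 180, plus liver and renal at day 60 if sampled then |
| Day 90 | Narrow, does not attend day 180 | No liver, renal or blood-count result | Liver and renal at day 60; no blood count |

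The laboratory gap can thus arise under either reading. The one step specified after stopping may be a telephone call, which yields no blood sample.

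**Step 4. AE review, set side by side.** The AE sentence covers days 60, 120 and 180 and makes no exception for those who stop. Outcome Measures monitors AEs for the whole study. The stop rule mentions neither AEs nor safety. On the narrow reading these agree; on the wide reading they conflict. The text does not choose between them.

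**Step 5. Does the stated reason reach safety data?** Every measure it names depends on the ON or OFF medication state. Liver, renal and blood-count tests and AE questions are not on that list, and the protocol attaches no medication state to them.

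**The case against.** The strongest reply is that the rule is limited by its own wording. It stops outcome assessments and lists only efficacy-type measures. The protocol uses separate terms for safety assessments, and the Harms section does so one paragraph earlier. AE assessment at each scheduled visit has no exception. The Consent section has every AE in the trial reported to the DSMB, treated and independently reviewed. The reference to a next planned visit suggests that visits may go on after stopping.

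Much of this stands. A reader might infer that the protocol orders no further safety blood test or AE review for anyone who stops. It does not say that. The sentence on laboratory timing applies to all participants and says nothing about those who stop.

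A reader might also infer that 19 to 24 participants will lack a safety panel. The documents do not support that either. The 14 discontinued participation, which may include withdrawals and losses that no wording would bring back for a sample. Arm and reasons are not given, and control-arm discontinuers had no Ayurveda exposure. Table 2 also gives liver and renal results at day 60 to those still in the study then.

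A further reply is that a journal article may leave early-termination procedures to the full protocol. That is fair for a missing early-termination visit taken alone. It does not dispose of a stop rule that is printed with unclear scope and a reason that does not fit safety data, nor of two laboratory schedules that disagree.

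**Conclusion.** The point holds in a limited form.

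- **Laboratory safety is the firmer part.** In the text, the only post-baseline liver, renal and blood-count sample is at day 180, and nothing secures it for someone who stops early. Such a participant may have no post-baseline laboratory result under the text, and no post-baseline blood count under Table 2.
- **The schedules contradict each other.** The text and Table 2 differ on liver and renal tests at day 60.
- **AE review is at risk from ambiguity only.** The documents do not state that it ends.

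On size, 14 of 58 (24.1%) have discontinued so far, against 20% allowed for. How many stopped for an adverse effect, from which arm, and how many lack a post-baseline result cannot be told from the documents. The projection of 19 to 24 among 80 assumes that the observed rates continue. The trial is exploratory and its safety analysis descriptive, so the harm would be to the credibility of the safety statement. With 11 participants continuing and 80 − 58 = 22 still to enrol, a clarification now would still be of use.

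**What to change.** Reconcile the Harms section with Outcome Measures and Table 2 by a short amendment:

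1. State that the stop applies to the ON/OFF-state efficacy assessments only. State that the safety laboratory tests and AE review already planned still apply, in both arms, to participants who stop or deviate and who remain contactable and consenting.
2. Use the contact already planned for recording the reason to complete the AE review too.
3. Make the laboratory schedule the same in the text and in Table 2.
4. Report laboratory safety separately for completers and discontinuers, by arm, with the number who have no post-baseline result.

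Which laboratory schedule is intended, the timing of any sample, and any clinical action on a result are for the sponsor and investigators to settle.

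The cost is one amendment and a few extra contacts or samples, drawing on tests and calls already planned. Some discontinuers may decline, so the gap will shrink but may not close.

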### Strategies for Improving the Fidelity of Care Providers and Adherence of Participants

The Ayurvedic intervention is standardized and will be administered uniformly as per the protocol. Participants will be screened for suitability before Panchakarma therapy, and the intervention will be withheld in cases of intolerance, fever, respiratory infection, or any other clinical contraindication. To ensure uniformity, all procedures will follow standard operating protocols, and participants will receive patient information leaflets detailing the interventions.

As panchakarma therapies are delivered in an inpatient or closely supervised setting by trained professionals, adherence will be monitored daily through direct supervision and treatment logs. Participants are required to maintain a compliance form to record the intake of both standard care and add-on oral Ayurvedic medications, which will be reviewed by the study team during follow-up visits. Furthermore, to promote participant retention and minimize missing data, follow-up will be reinforced through periodic telephonic contact between scheduled visits.

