### Statistical Analysis

All analyses will be performed using SPSS software. The primary outcome, change in MDS-UPDRS Part III score from baseline to 24 weeks, will be analyzed using a mixed model for repeated measures with treatment, time, and treatment×time interaction as fixed effects and baseline values as covariates. LEDD will be included as a time-varying covariate to account for dopaminergic medication effects. Results will be reported as least-square mean differences with 95% CIs. The main analysis will follow a modified intention-to-treat approach including all randomized participants who receive at least one dose of the assigned intervention, whereas a per-protocol analysis will be performed as a sensitivity check on participants who complete ≥80% of scheduled therapies and medication adherence.

Missing data will be handled under the assumption of data missing at random using the mixed model for repeated measures model, which uses all available data without imputation. Additional sensitivity analyses, including multiple imputation and complete case analyses, will be performed to evaluate the robustness of results. The secondary outcomes will be analyzed using appropriate mixed or generalized linear models and interpreted as exploratory. Descriptive statistics will summarize categorical variables as frequencies and percentages, and continuous variables as mean (SD), median (IQR), and range.

Predefined subgroup analyses will explore whether treatment effects differ by baseline Hoehn and Yahr stage (≤3.0 vs >3.0), disease duration (<5 vs ≥5 y), age (<65 vs ≥65 y), baseline LEDD (≤ median vs >median), and presence of dyskinesia. Interaction terms will be tested using mixed effects models, and the results will be interpreted as exploratory. Sensitivity analyses will include assessing participants with stable dopaminergic doses (<10% LEDD change) and testing the interaction between treatment allocation and LEDD change to explore medication-dependent effects. Safety analyses will be descriptive, summarizing AEs and serious AEs by treatment group.

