## Results

As of August 2025, a total of 259 patients with PD have been screened for eligibility, of whom 58 participants have been successfully enrolled in the trial; among these, 33 participants have completed the intervention and follow-up assessments, 14 have discontinued participation, and 11 are currently continuing in the study. Recruitment and follow-up are ongoing, and the trial is scheduled for completion in September 2026.

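### Outcome assessment ends when a participant stops or deviates from the intervention, which conflicts with the modified intention-to-treat analysis and leaves off-treatment outcomes unobserved

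*Protocol article*

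**What the plan says.** The rule is in the protocol article, under Harms: AE Collection, Assessment, Reporting, and Management: "For participants who discontinue or deviate from the intervention protocol, no further outcome assessments will be conducted". The reason follows directly: "as the primary outcome (MDS-UPDRS Part III) requires evaluation in both ON and OFF medication states", with several other tests done in the OFF state. The same paragraph still expects contact with these participants, since their reasons "will be systematically documented either during the next scheduled visit or through telephonic communication".

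The Statistical Analysis section plans a "modified intention-to-treat approach including all randomized participants who receive at least one dose of the assigned intervention". On missing values it says: "Missing data will be handled under the assumption of data missing at random using the mixed model for repeated measures model". It then adds: "Additional sensitivity analyses, including multiple imputation and complete case analyses, will be performed to evaluate the robustness of results". A per-protocol analysis, at 80% or more of scheduled therapies and medication adherence, is a further check.

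The section on fidelity and adherence says that, "to promote participant retention and minimize missing data, follow-up will be reinforced through periodic telephonic contact between scheduled visits". The Results section reports that, of 58 enrolled by August 2025, "33 participants have completed the intervention and follow-up assessments, 14 have discontinued participation, and 11 are currently continuing in the study".

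**The concern.** An intention-to-treat analysis, modified or not, compares participants as randomised, whatever they did afterwards. That requires outcomes from people who stopped. Here the protocol itself removes those outcomes, and the trigger is non-adherence. The Harms section gives adverse effects and lack of perceived benefit as examples of reasons for non-adherence, so missingness related to outcome is foreseeable.

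At stake is what the reported treatment difference means. Without off-treatment scores, a model that assumes missing at random fills the gap with what participants would have scored had they carried on. If stoppers lose some or all of the benefit, the result is more favourable than the effect of being assigned to the regimen. A reader would take it for the latter because of its label. Visits that are missed cannot be recovered later.

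**Working it through.** **1. Does the stated reason support the rule?** The Outcome Measures section defines OFF as 12 hours after the last dopaminergic medication and ON as 1 hour after the first morning dose. The sections on assignment and on Group A place that medication with the treating neurologist, and Group B receives the same conventional care plus Ayurveda. Stopping the Ayurveda regimen therefore does not by itself prevent ON/OFF testing. The reason also cannot cover MDS-UPDRS Parts I and II, which are done in the ON state only, or the sleep scale and plasma cytokines, for which no OFF state is stated. Contact is not the obstacle either, because reasons may be collected at the next scheduled visit.

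**2. What can the planned analyses still show?**
- *Mixed model:* it runs, using day-60 and day-120 scores obtained before stopping. Only those who stop before day 60 contribute no post-baseline score. No off-treatment score is ever observed.
- *Per-protocol:* it drops later stoppers whose early visits the main analysis keeps, so the two differ somewhat. At day 180, however, both rest mainly on adherers. If any deviation triggers the rule, everyone with a day-180 score is an adherer. Because no threshold is given, the overlap cannot be fixed exactly.
- *Complete case and standard multiple imputation:* the first needs missing at random or something stronger, and the second assumes it. Neither tests a departure from it.

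**3. How many participants are affected so far?** Inputs from Results: 33 completed, 14 discontinued, 11 ongoing; 33 + 14 + 11 = 58.
- Share of enrolled: 14/58 = 24.1%.
- Share with known final status: 14/(33 + 14) = 14/47 = 29.8%, exact 95% CI 17% to 45%.
- Final range for these 58: 14/58 = 24.1% if none of the 11 stops, to 25/58 = 43.1% if all do.

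**4. Is there a shortfall against the plan's own numbers?** The Sample Size section takes 28 evaluable per group and recruits 40, citing 20% attrition. The 40 is not reproduced at 20%: 28/(1 − 0.20) = 35. It is reproduced at 30%: 28/(1 − 0.30) = 40. Applying 29.8% to 80 leaves 80 × 0.702 = 56, or 28 per group. Taking the stated 28 as given, there is no shortfall.

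**5. How far apart could the two effects be?** Assumptions, none of them in the documents: effect Δ while on treatment, a proportion p of Group B stops, and stoppers keep a fraction r of the benefit. The effect regardless of adherence is Δ × [1 − p(1 − r)]. The missing-at-random analysis targets Δ. The ratio is 1/[1 − p(1 − r)].

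| p | r = 0 | r = 0.5 | r = 1 |
|---|---|---|---|
| 20% | 1/0.80 = 1.25 | 1/0.90 = 1.11 | 1.00 |
| 30% | 1/0.70 = 1.43 | 1/0.85 = 1.18 | 1.00 |
| 40% | 1/0.60 = 1.67 | 1/0.80 = 1.25 | 1.00 |

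**The case against.** The strongest reply has four parts.

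- **The plan is for a modified analysis, and its model uses all available data.** This stands: the analysis can be carried out. What is lost is an estimate that holds regardless of adherence.
- **Part of the gap is a difference of target, not bias.** This also stands. An effect under continued treatment is a legitimate quantity if it is named as such and missing at random is plausible. Here it carries an intention-to-treat label, and the listed reasons for non-adherence put the assumption in doubt.
- **The documents do not show that the rule caused the losses.** This stands. The 14 discontinued participation, and some may have withdrawn or been lost, which would leave them missing under any rule. No figures by arm are given. Group B has the more demanding regimen, but the compliance form covers standard medication too, so control participants can also deviate.
- **The list of sensitivity analyses is open, and a separate analysis plan may extend it.** This stands for the choice of method. It does not help with the follow-up rule, because no analysis plan can restore data that the protocol says will not be collected.

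The trial calls itself exploratory, which lowers the stakes somewhat. It is also designed as a superiority trial and is meant to inform larger ones, so the meaning of its estimate still matters.

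**Conclusion.** The follow-up rule and the modified intention-to-treat analysis contradict each other, and the reason given does not justify the rule. Off-treatment outcomes go unobserved, so an effect regardless of adherence can be obtained only through assumptions that the data cannot test. The named checks do not examine those assumptions.

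The size is uncertain. Observed discontinuation is 24.1% of those enrolled, or 29.8% of those with known status. The second figure may run high, because a discontinuation is known sooner than a 180-day completion. Deviators who did not discontinue would add to either. The illustrative overstatement runs from nothing, if stoppers keep all the benefit, through 11% to 25% if they keep half, to 25% to 67% if they keep none, for 20% to 40% stopping in Group B.

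A reader might infer more than the documents support:
- *That intention-to-treat analysis becomes impossible.* The model runs on earlier visits.
- *That about 30% of participants lack a day-180 outcome because of this rule.* The 30% uses the smaller denominator, and the cause of each loss is not reported.
- *That safety laboratory tests stop as well.* The rule speaks of outcome assessments and lists efficacy and neurophysiological tests. Safety tests are described separately, and the text does not say that they end. It should say which applies.

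**What to change.** Amend the Harms and Statistical Analysis sections so that they agree:

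1. Separate stopping or deviating from the intervention from withdrawing from the study.
2. Continue the scheduled day-60, day-120 and day-180 outcome assessments for every randomised participant who consents, whatever their adherence, and include these scores in the primary analysis.
3. Apply this to ongoing and future participants, and report how many were followed under the present rule. In August 2025 that meant 11 ongoing plus 80 − 58 = 22 not yet enrolled, 33 in all.
4. State explicitly that safety laboratory tests and adverse event follow-up continue after stopping.
5. State which effect the primary analysis estimates. For participants still without data, add a reference-based or delta-adjusted sensitivity analysis.

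The cost is an amendment, possibly renewed consent, and extra visits at the same site with existing staff. If the 33 stop at the rates seen so far, that is about 33 × 0.241 = 8 to 33 × 0.298 = 10 people, with at most three visits each, plus any deviators who did not stop. The trial would contain two follow-up regimes, which must be reported. Some participants will decline, and the estimate may be less favourable.
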